### C) Suitability Assessment of Materials of (SAM) and Readability Assessment of Materials (RAM)

In order to check the suitability as well as readability of educational content of mental health literacy program guide, SAM and RAM will be used with the first one checks the suitability and the other one checks the readability of materials [31].

### Suitability Assessment of Materials of (SAM)

SAM evaluates written materials according to 22 criteria organized into six categories: "Content," "Required Literacy Level," "Graphics," "Layout and Typography," "Learning Stimulation and Motivation," and "Appropriateness." Each factor is scored as excellent (2 points), suitable (1 point), or non-suitable (0 points). Not applicable are factors that do not apply to a given material. The maximum possible score is 44, but 2 points are subtracted for factors that are not relevant. The overall SAM score is made by adding up the scores for each item. Then, this score is turned into a percentage by dividing the total SAM score by the total possible score for that particular subject. This material is classified as non-suitable (0%-39%), suitable (40%-69%), or excellent (70%-100%) [31].

### Readability Assessment of Materials (RAM)

RAM evaluates the difficulty of reading an educational media into three categories: specialized content (score range 0–6), misspellings (score range 0–6), and typographical mistakes (score range 0–6). The range of scores in media readability evaluation is 0 to 18, with a score of more than 10 being satisfactory [31].

### The guide cymru's teacher evaluation

The school-based mental health literacy program will be evaluated by 20 trained teachers using the evaluation checklist that will be designed. In this way, the teacher will complete the evaluation checklist following each training session. On the basis of the teachers' feedback, the curriculum will be evaluated.

### Reliability and Validity of General Mental Health and Attitudes to Mental Disorders/Illnesses

At this point, the tool will be translated in compliance with IQOLA standards after obtaining the developer's permission [24]. Two English language professionals translate the instrument into Persian, and then the study team's researchers and mental health experts review, modify, and make the necessary changes. The translation will then be back translated into English by two experts. Following assessment by the study team's researchers, the English translation created at this step will be sent to the tool maker via email to validate the correctness of the translation and the right understanding of the tool's items and after the approval, the Persian version of the instrument will be psychometrically assessed at this stage [30].

### Determining face validity:

The questionnaire's face validity will be assessed using two qualitative and quantitative methodologies. To examine the face validity qualitatively, 10 experts in the fields of health education and promotion, psychology, psychiatry, and biostatistics will assess the degree of difficulty, suitability, and ambiguity and make any required modifications. Furthermore, the item impact method will be utilized to test the face validity quantitatively. As a result, the 5-valued Likert scale runs from 5 to 1 point for each instrument item, with the possibilities of very important, rather important, moderately important, somewhat important, and not important at all. In addition, ten experts will be asked to assess the significance of each item for the provided structure based on their past knowledge. Using the following formula, the impact score for each item is then calculated. All items greater than 1.5 will be regarded as acceptable.

$$\mathrm{Impact}\;\mathrm{Score}\:=\:\mathrm{Frequency}\;(\%)\:\times\:\mathrm{Importance}$$

I

The proportion of respondents who gave the item a score of 4 or 5 represents frequency, and the average importance score based on a 5-point Likert scale represents importance. If the impact score exceeds 1.5, the item is considered eligible for further study and is kept [29].

### Content Validity

The content validity will be determined using two qualitative and quantitative methodologies. As part of the qualitative review of the content, the final translated version of the questionnaire will be presented to ten psychometric experts to provide the required feedback after a qualitative examination of the tool based on grammar, usage of relevant words, placement of phrases in the proper location, and appropriate scoring. Also, the Content Validity Ratio (CVR) and the Content Validity Index (CVI) will be used to assess the content validity quantitatively.

With CVR, the necessity of an item is assessed by professionals so that only the most significant and correct items are chosen and CVI evaluates the clarity, adequacy, or relevance of the items with respect to the researcher's objective are evaluated from the perspective of experts, which aids in designing the items in the most effective manner to measure the content. In order to determine the CVR, the group of experts is requested to assess as well as score each item's necessity based on the three-part Likert spectrum (necessary, useful but not necessary, and not necessary). It is therefore possible to ensure the selection of the most crucial and accurate content based on the scores obtained for each item.

In addition, to check the CVI, following distribution of the tool to ten psychometrics specialists, the score obtained from their opinions on the relevance, clarity and simplicity of each item will be calculated based on a four-part Likert scale. Therefore, it is possible to ensure the selection of the most relevant, simple and clear items. The minimum acceptable value for the CVI index is 0.79, and any item with a CVI index less than 0.79 should be eliminated [30].

### Tool reliability

The consistency of an instrument over time is referred to as its reliability, and the reliability test focuses on three aspects of internal consistency, stability, and equivalence. Internal consistency or stability is measured with Cronbach's alpha, and stability over time is measured with the test–retest method [32]. Two methods of internal consistency and stability will be employed in this study.

### Internal consistency/Cronbach’s alpha

Internal consistency, which indicates the agreement between the instrument's various dimensions, is a common method for determining its reliability. By splitting an instrument in half and comparing the two halves together, or by computing the Cronbach's alpha coefficient, the internal consistency of the instrument can be determined. In this study, Cronbach's alpha coefficient will be calculated after construct validity. The minimum acceptable level of alpha will be 0.7 [33].

### Stability/test–retest

Stability refers to obtaining identical scores from a group of individuals at two distinct time points and represents the degree of change over time. Thus, the stability of a tool is evaluated over time. Utilizing the test–retest method and calculating the intraclass correlation index, stability is evaluated. In the present study, in order to determine the consistency between the modules of the final program guide based on the test–retest criterion, the guide will be completed in two stages by 30 participants with an interval of two weeks. Then, using the intra-cluster correlation index (ICC), the scores obtained in these two steps will be compared [34]. The ICC rate ranges from zero to one, and the closer it is to one, the higher the reliability. According to China, a tool must have a reliability coefficient of at least 0.6 to be considered acceptable [35, 36].

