#### Study phases

Followings are the procedures for conducting the study in two phases:

Phase 1: Translation and cultural adaptation of the mental health literacy program* "The Guide Cymru".*A) Translation and cultural adaptation of *"The Guide Cymru".*b) Accreditation of the school-based mental health literacy training program "The Guide Cymru".c) Suitability and readability assessment of materials (SAM & RAM).d) Validity and reliability of general mental health knowledge and attitudes related to mental disorders/illnesses.Phase 2: Implementation of the educational program and evaluation of the school-based mental health literacy program *"The Guide Cymru".*Step 1) Pre-test.Phase 2) Empowering teachers in mental health literacy based on school-based mental health literacy program *"The Guide Cymru".*Step 3) Implementation of an educational program for students based on school-based mental health literacy program *"The Guide Cymru".*step 4) Evaluation of the impact of school-based mental health literacy program *"The Guide Cymru".*

## Implementation of phase 1

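### The test-retest step names the programme guide, which has no respondent score, where the protocol's own plan calls for the knowledge and attitude questionnaires

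*Protocol article*

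**What the plan says.** Step d of Phase 1, in the Study phases section of the protocol article, is "Validity and reliability of general mental health knowledge and attitudes related to mental disorders/illnesses". The section on translating and culturally adapting the guide repeats that these two questionnaires, which come with the guide, will be tested for validity and reliability.

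The section that carries out step d is headed "Reliability and Validity of General Mental Health and Attitudes to Mental Disorders/Illnesses". After translation and approval by the developer, it says, "the Persian version of the instrument will be psychometrically assessed at this stage". Face validity, content validity and reliability follow. Under Tool reliability the commitment is explicit: "Two methods of internal consistency and stability will be employed in this study".

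The Stability/test–retest section then changes the object. Its stated aim is "in order to determine the consistency between the modules of the final program guide based on the test–retest criterion", and its procedure is that "the guide will be completed in two stages by 30 participants with an interval of two weeks". The analysis is that, "using the intra-cluster correlation index (ICC), the scores obtained in these two steps will be compared". The acceptance rule is that "a tool must have a reliability coefficient of at least 0.6 to be considered acceptable".

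**The concern.** The retest is assigned to the wrong object. A test-retest ICC needs the same score from the same people on two occasions, with nothing in between that is meant to move it. The guide meets neither condition: it is a taught curriculum with no respondent score, and working through it is intended to change what people know. Consistency between modules is also a different property from stability over time, which the same section defines as the same people scoring the same at two time points.

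What is at stake is the stability evidence for the two newly translated questionnaires. The trial gives them to students before the programme, after it and again two months later, and the evaluation section relies on comparing a student's scores across those occasions. Anyone who follows the stability section literally would run a study that cannot produce the evidence promised under Tool reliability, and the 0.6 rule would be applied to something that is not an outcome measure.

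**Working it through.** The documents give no ICC result and no derivation of the 30, so there is no stated figure to reproduce. The check is a comparison of sections of the protocol article.

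**1. What is to be shown reliable.** Study phases (step d), the translation section and the heading of the psychometric section all name the knowledge and attitude questionnaires. Tool reliability promises both internal consistency and stability.

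**2. What is retested.** Stability/test–retest names the guide twice, once in its aim and once in its procedure.

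**3. Does the guide have a score?** The description of The Guide Cymru calls it a resource taught in 8 to 12 class hours. Step 3 of Phase II describes six modules taught over eight to ten sessions. The only ratings planned for it are appraisals of the material: content validity ratio and index, the suitability and readability assessments, the four-question expert checklist and the teacher checklist. None of these is a score that a participant earns by completing the guide.

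**4. Is a guide retest planned elsewhere?** The section on the validity of the programme says that tools in general must be reliable. Its list of what will be determined for the guide, however, is face validity, content validity, feasibility, acceptability and educational impact. The stability section is therefore not carrying out a guide-reliability plan set there.

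**5. Are the questionnaires retested elsewhere?** No. Internal consistency is planned, with Cronbach's alpha of at least 0.7. The questionnaire section cites an alpha of 0.71 from an earlier study. Neither is a test-retest figure.

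Items 1 and 2 contradict each other. By items 3 to 5, following the text literally gives an ICC without a defined input and no stability estimate for either questionnaire.

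**6. What the corrected step would deliver.** The form of ICC is not stated, so a one-way single-measure ICC is assumed, with n = 30 people and k = 2 occasions. For an observed ICC r:

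- F = (1 + (k − 1)r) / (1 − r). At r = 0.60, F = 1.60 / 0.40 = 4.00.
- The 97.5% points of the F distribution are 2.083 on (29, 30) and 2.092 on (30, 29) degrees of freedom.
- F_L = 4.00 / 2.083 = 1.92 and F_U = 4.00 × 2.092 = 8.37.
- Lower limit = (F_L − 1) / (F_L + k − 1) = 0.92 / 2.92 = 0.32.
- Upper limit = (F_U − 1) / (F_U + k − 1) = 7.37 / 9.37 = 0.79.

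| Observed ICC | 95% interval |
|---|---|
| 0.60 | 0.32 to 0.79 |
| 0.70 | 0.46 to 0.84 |
| 0.80 | 0.62 to 0.90 |

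Of these three values, only 0.80 has a lower limit above the 0.6 floor.

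**The case against.** The strongest reply is that this is a slip of wording and not a design decision. The questionnaires come with the guide, the knowledge items follow its six modules, and the stability section itself speaks of a tool and of scores. It also sits inside the section on the questionnaires. On that view any reader would understand that the questionnaires are meant. The explanation is probably right, and it limits the weight of the point. It does not remove it: the aim speaks of modules of the final programme guide, which points away from the questionnaires, and no other text says what will be completed twice.

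A second reply is that other reliability evidence exists. That stands: Cronbach's alpha is planned for the questionnaires, so only stability over time is left uncovered.

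A reader might also infer more than the documents support, in four ways:

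- **Change could not be told from instrument drift.** Drift common to both arms would show in the randomised control group and cancel in a between-arm comparison. An ICC is not the safeguard against it, and a consistency-type ICC ignores a uniform shift altogether. The Data analysis section names a paired before-and-after test, but that is a separate matter.
- **Effects would shrink to about 77% of their true size.** That figure is √0.60 and treats the acceptance floor as the actual reliability, which no section supports. A retest would measure the reliability, not change it.
- **The Mental Health Literacy Scale must be retested too.** Step d covers only the knowledge and attitude questionnaires.
- **The 30 must come from schools outside the 20 in the trial.** Nothing in the article requires this, and it would be more than a change of wording. An article may also leave details of these participants to the full protocol.

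**Conclusion.** The point holds as an internal contradiction. The stability section retests the guide, while the rest of Phase 1 commits to testing the reliability, including stability, of the Persian knowledge and attitude questionnaires. This is text that is wrong as written, not detail left to a fuller document.

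Taken literally, the number of test-retest estimates for the 28-item and 8-item scores is zero, and the planned ICC cannot be computed from anything the article defines. No bias in the treatment comparison and no loss of power follows from this. The conclusion rests on the article's text alone. The intervals shown above rest on the assumed form of ICC and describe the precision of the corrected step; they are not part of the defect. The correction should be made, but the trial does not stand or fall on it.

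**What to change.** Reword the Stability/test–retest section so that:

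- the 30 participants complete the Persian general knowledge and attitude questionnaires twice, two weeks apart;
- they are preferably of the target age, 13 to 15, and not exposed to the guide between the two occasions;
- an ICC with its 95% interval is reported for each total score, with the form of ICC named;
- the 0.6 rule is applied to each of the two scores;
- the ICC for guide modules is dropped.

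If the retest has not yet been run, the cost is a change of wording with the same number of people and the same interval. Parts of the preparatory work are described in the past tense. If the retest has already been done, the article should state what was completed twice; if that was not the two questionnaires, new data would be needed. The remaining drawback is the limited precision from 30 people, so each interval should be read beside the 0.6 rule.

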### Phase II: Implementation of the training program and evaluation of the school-based mental health literacy program *"The Guide Cymru"*

Step 1) Pre-test.Phase 2) Empowering teachers in mental health literacy based on *the Guide Cymru.*Step 3) Application of a training program for students based on *the Guide Cymru.*Phase 4) Evaluation of the impact of *the Guide Cymru'*s school-based mental health literacy program.

### Implementation of Phase II

#### Step 1) Pre-test

This component is intended to help the teacher with self-study before using the guide in the classroom. Participating in the pre-test assists in identifying areas where the teacher's knowledge base needs to be expanded. Following the participation, questions with incorrect answers are recorded. Then, the teacher's mental health literacy will be strengthened using the guide's educational resource. The post-test is administered following the completion of the teacher's mental health literacy empowerment. The pre- and post-test questionnaires for teachers will be mental health literacy and mental health general knowledge questionnaires. Questionnaires will be completed again two months later.

Teachers (control and intervention groups) will complete the Mental Health Literacy Scale (MHLS) and general mental health knowledge prior to the implementation of the program. Also, Students (control and intervention groups) complete questionnaires assessing mental health literacy, general knowledge of mental health, and attitudes toward mental disorders, in addition to a demographic information form. Lastly, the participants will decide when the best time is to hold the educational intervention classes.

### Phase 2) Empowering teachers in mental health literacy based on* the Guide Cymru*

The purpose of this component is to provide the teacher fundamental knowledge on mental health and mental diseases so they may utilize the resource more effectively in the classroom. The source guide is comprised of six modules including: 1) Stigma of Mental Illness, 2) Understanding Mental Health and Mental Illness, 3) Information About Specific Mental Illnesses, 4) Experiences of Mental Illness and the Importance of Family Communication, 5) Seeking Help and Support, and 6) The importance of positive mental health. Teachers in the intervention group will attend a two-day training session for the six-module school-based mental health literacy program as well as will get the he resources and content of the Persian-language version of the school-based mental health literacy program. Furthermore, The educational content of the Persian version of the website http://teenmentalhealth.org, which is a rich repository of original and supplementary educational materials based on six educational modules will be provided to teachers through available messengers.

### Step 3: Application of an educational program for students based on the Guide Cymru

Prior to the start of study, written consent will be obtained students' parents. Teachers will provide informed consent forms to parents. To keep the confidentiality and anonymity, consent forms will be gathered, and the study team will develop an identification code for each student, which will be completed by teachers. It is worth mentioning that this code will be will be used in student evaluation. Participants are also assured that their personal information will be kept strictly confidential. The evaluation is based on three questionnaires measuring mental health literacy, general knowledge of mental health, and attitudes toward mental disorders, allowing the teacher to assess the significant dimensions of mental health literacy. Before teaching the guide in the classroom, the pre-test will be administered; following the completion of the sixth module, the post-test will be administered again; and two months later, the questionnaires will be administered once more. Students will attend sessions on the specified day and time depending on the allocated groupings. Following the pre-test, a qualified teacher will lead an educational content session of the school-based mental health literacy program based on the six modules under the supervision of the researcher and psychologist. The Guide training consists of six modules taught sequentially over the course of eight to ten sessions. The modules are constructed in such a manner that each one is conducted in 60-min lessons. Among all modules of the Guide, the third module is the longest and most informative module, requiring more teaching time than the others. As a result, three 50-min intervals will be allotted to this module. In the control group, the general content of the Guide Cymru educational program will be presented by a psychological expert with the coordination of teachers and students. Finally, after the evaluation of the school-based mental health literacy program, teachers and pupils in the control group will receive the Guide Cymru program guide.

### Phase 4) Evaluation of the impact of Guide Cymru's school-based mental health literacy program

According to study of improvements in students’ mental health literacy with use of a mental health curriculum in Canadian schools [13], mental health literacy, general knowledge of mental health and attitudes related to mental disorders of students and teachers before and after the implementation of the educational intervention and with a 2-month follow-up were evaluated and the results will be compared before, immediately after, and two months after the educational intervention. By comparing a student's pre-test, post-test, and two-month post-test scores, this method of evaluation enables a precise determination of student's learning.

### Data Collection Method

In this study, data will be gathered through questionnaires on mental health literacy, general knowledge of mental health, and attitudes toward mental disorders, as well as demographic information.

### Questionnaire 1) Mental Health Literacy Scale (MHLS)

The Mental Health Literacy Scale (MHLS) was introduced by O'Connor and Casey in 2015 and includes six attributes of the ability to recognize specific disorders, knowledge of professional help available, knowing how to seek mental health information, knowledge of self-treatments, knowledge of risk factors and causes, and attitudes that promote recognition and appropriate help-seeking [7]. These features were examined and compared to the findings of Jorm [37] and Griffiths, Christensen [38] studies. Nejatian, Tehrani [39] evaluated and modified the 35-question questionnaire version of the scale. After the evaluation, six questions were removed and the modified version of the MHLS with 29 items and six attributes was confirmed. For the reliability, McDonald's Omega coefficient and Cronbach's alpha coefficient were calculated to be 0.797 and 0.789, respectively.

